The primary aims are to: 1) conduct a factorial experiment (optimization trial) to test the main effects of each of the four Suubi intervention components and combinations of components (interactions) on viral suppression (primary outcome); 2) Test mediators and explore moderators that explain and modify the relationship between each of the four Suubi intervention components and viral suppression; and 3) compare the cost and cost-effectiveness of each of the four Suubi intervention components and every combination of components.

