### Randomization

Aim 1 is a 2^4^ factorial experiment resulting in 16 unique conditions representing all possible combinations of the 4 components. Randomization will be at the level of health clinics (*N* = 48 and geographically distant from each other) to prevent contamination across conditions. Clinics will be randomized to one of the 16 conditions, with 12 ALHIV (aged 11–17 years) enrolled per clinic, yielding main effects and interaction effects for the 4 components on sustained viral suppression (primary outcome) [86]. Refer to Fig. 3 (SPIRIT flow chart).

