### Data analysis plans

Effect coding is used to produce uncorrelated main effect estimates, unbiased standard errors, and clearer interpretations of interactions between components in factorial designs. The single covariate of randomization stratum with four levels reflecting the combination of two binary variables: 1) ALHIV population size (medium size vs. large) and 2) geographical location (rural vs. urban), to ensure balance on those variables. Our preliminary analysis will focus on assessing balance in assignment to conditions. The stratified restricted cluster randomization is expected to produce balance across the 16 conditions [132]. We expect to have equal cell sizes to estimate the main effects and interactions and equal percentages of ALHIV population sizes and geographical locations in our main comparisons. For thoroughness, we will check for imbalances across the four component comparisons (e.g., percent of rural vs. urban participants in the financial literacy versus no peer financial literacy comparison), rather than across 16 conditions because recall that a 2^4^ factorial design is not a 16-arm comparison. In the unlikely event that an imbalance does occur by ALHIV population size and/or geographic location, we will use propensity score matching (i.e., a conditional probability of having one component delivered versus another) with baseline covariates collected in our survey to estimate the primary outcome under the counterfactual assumption of balanced groups [133–135]. The proposed analyses and syntax code will be documented and made available on request to enable review, transparency, and results reproducibility.

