The goal is estimating main effects for sustained viral suppression. Factorial designs with continuous, normally-distributed outcomes measured cross-sectionally are often evaluated using an Analysis of Variance (ANOVA), which is a special case of a general linear model (GLM). For.analyses with clustering (within-subject correlations) and non-normal outcomes (e.g., sustained viral suppression), generalized estimating equations (GEE) can be used instead of ANOVA [136–138]. Recall that our primary outcome is a single computed variable of sustained viral suppression—all 1 s on the Y variable at 12-, 24-, and 36-month follow-up assessments. Thus, we are using GEE, not based on repeated measures across time, but because of clustering that will occur through the cluster randomized trial (CRT) design approach we are using. Participants who visit the same clinic may not be statistically independent [137]. Thus, GEE can properly account for the correlation of participants within the same clinic by using robust standard errors to correct inferences, even if the chosen correlation structure remains slightly misspecified. Moreover, within-clinic correlations of outcomes are considered nuisance parameters, not quantities of interest to be modeled explicitly [136]. In GEE, we will a priori specify a working correlation structure—specifically the exchangeable correlation structure (compound symmetry assumption)—given the assumption of a balanced factorial design and a single level of clustering by clinic [139]. Alpha (α) will be set at 0.05 for estimating main effects, which are orthogonal (i.e., independent) of each other. As detailed by Kahan and Morris [140], stratification during the randomization process must be accounted for in the primary analysis as it may lead to correlations among the participants in each cell. Uncorrected, this would bias standard errors estimates, producing wider confidence intervals, a lower Type I error rate, and affect statistical power. Thus, all analyses will be adjusted by randomization stratum to produce unbiased estimates.

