Factorial designs are innovative in their ability to estimate how two or more components interact, which is not possible with a multi-component packaged intervention. Following the MOST framework, α will be set to 0.10 for all interaction effects, which is justified by the decision-priority perspective [141] guiding this study. To enhance rigor, we will test if interactions among components yield additive and/or synergistic interactions. Additional exploratory analyses will add sex as a covariate and extend each of the previously-described analyses to include interactions of each effect with sex. We propose the following hypotheses for the mediation analyses (also depicted in conceptual model, Fig. 2).

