### Economic evaluation

Following standard practice, we will measure costs for each of the 16 combinations on a per-person basis using an activity-based approach. Costs of the interventions include all program costs, such as YSA savings match, costs for the FLT workshops, Suubi Cartoon, engagement with role models, training, volunteers and donated materials, and running the programs. Research costs are excluded. Costs will be divided by effects to determine efficiency in CEA. To compare the value of two mutually exclusive approaches, a typical RCT reports the cost per added gain as the incremental cost-effectiveness ratio (ICER = (C1-C0)/(E1-E0)), where C=cost, E=effect, 1=intervention, and 0=baseline. The ICER is often compared to other such estimates in the literature and to a decision-maker’s threshold of acceptability to guide policy. For MOST and the factorial design, CEA decisions and optimization are more complex [146]. First, we will test whether any of the 4 components have interacting costs or effects—i.e., economies or effects of scale (If there are no significant interactions, decisions to adopt each of the combinations can be made independently). Next, interventions will be ordered by increasing cost, and we eliminate any “dominated” combinations which are more costly but less effective than a cheaper strategy. Finally, we will compute ICERs for comparison to the literature (such as our past studies [77, 78]) and for assessment as policy options, such as comparing to pre-exposure prophylaxis. Our baseline CEA will focus on ICERs with no budgetary threshold. Next, we will use the MOST framework to assess ICERs while placing constraints on affordability and scalability to select the best possible combination for various levels of a decision-maker’s preferences for affordability and scalability alongside efficiency. Confidence intervals will be generated using bootstrapping and Monte Carlo simulations.

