### Power analysis

Power analyses for our proposed primary analysis was generated using the multilevel logistic regression module for proportions in a 2-level hierarchical design in NCSS PASS 21 [147]. We set the base rate of sustained viral suppression to 50% based on MPI [name]’s Suubi-Adherence study. We assumed *N* = 576 participants recruited from 48 clinics and set α = 0.05, power = 0.80, and the intracluster correlation (ICC) due to clustering of participants within clinics at 0.024 based on data from MPI [name]’s Suubi-Adherence study. We conservatively assumed 20% attrition (*N* = 480). The minimum detectable odds ratio is 1.77, which corresponds to a minimum raw proportion difference of 14% and a standardized effect size of 0.28, which is between a small to medium effect size. For Specific Aim 2, the only difference in power calculations was we set the base rate of sustained viral suppression to 75% and the ICC to 0.038 based on 12-month achieved VL suppression data from MPI [name]’s Suubi-Adherence study. Under these conditions, the minimum detectable indirect effect odds ratio is 1.80, which is between a small and medium effect size [148].

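### With 48 clinics and only clinic-level regressors, the GEE robust standard errors need a named small-sample correction; without one, main-effect type I error is about 8% to 14% against the stated 5%

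*Protocol article*

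**What the plan says.** In the Protocol article, Randomization states "Clinics will be randomized to one of the 16 conditions", with 12 adolescents "enrolled per clinic, yielding main effects and interaction effects for the 4 components on sustained viral suppression". Power analysis confirms "participants recruited from 48 clinics". The primary aim (Background) is to "test the main effects of each of the four Suubi intervention components and combinations of components (interactions) on viral suppression".

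Data analysis plans chooses GEE with an exchangeable working correlation, clustered by clinic, and says that "GEE can properly account for the correlation of participants within the same clinic by using robust standard errors to correct inferences". Main effects are tested at 0.05; for interactions, "α will be set to 0.10 for all interaction effects". The adjustment variable is "The single covariate of randomization stratum with four levels", and it enters every analysis. The section discusses biased standard errors only as a result of ignoring stratification. It does not discuss the number of clusters, a small-sample correction or a reference distribution.

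Economic evaluation uses the interaction tests as a decision step: "If there are no significant interactions, decisions to adopt each of the combinations can be made independently".

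**The concern.** The ordinary sandwich variance is a large-sample estimator in the number of clusters. When the number of cluster-level parameters is not small compared with the number of clusters, it is too small on average, and a normal reference adds to the error. Here treatment and stratum vary only between clinics, so 48 clinics, not 576 participants, are the independent units. The stratum adjustment itself adds three more clinic-level parameters.

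At stake are the error rates that the plan announces. False main effects and false interactions would reach the optimisation step more often than 0.05 and 0.10 suggest, and the condition for judging components independently would be met less often.

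**Working it through.** **Inputs (Protocol article).** 48 clinics with 12 participants each; 16 conditions, so 48/16 = 3 clinics per condition if cells are equal, as the plan expects; base rate 50% and ICC 0.024 (Power analysis); alpha 0.05 and 0.10; four strata. Missing outcomes count as failure (Primary outcomes), so each clinic keeps 12 in the analysis. Assumptions of mine: two-sided tests, and strata defined at clinic level.

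**The plan's own power figure.** With N = 480, there are 240 participants per level in 48 clinics of 10. The design effect is 1 + (10 − 1) × 0.024 = 1.216, so the effective n per level is 240/1.216 = 197.4. Two-sided 0.05 and 80% power give a minimum detectable odds ratio of 1.77 and a difference of 13.9 points. The stated 1.77 and 14% are reproduced, using a normal reference.

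**Parameter counts (p).**
- Main effects and strata: 1 + 4 + 3 = 8.
- Adding six two-way interactions: 14.
- Full factorial and strata: 16 + 3 = 19.

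**Analytic approximation.** The uncorrected variance is too small by about (48 − p)/48. Standard errors are then too small by 1 − √(40/48) = 9%, 1 − √(34/48) = 16% and 1 − √(29/48) = 22%. Type I error is about P(|t on 48 − p df| > z × √((48 − p)/48)). For p = 19 at 0.05 the cut-off is 1.960 × 0.777 = 1.523, and the probability on 29 df is 0.138.

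**Simulation under the null.** 4,000 trials per model, beta-binomial outcomes, effect coding. With equal clinic sizes and clinic-level covariates, exchangeable GEE reduces to logistic regression with a cluster sandwich.

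| Model | p | Test (nominal) | Analytic, uncorrected | Simulated, uncorrected z | Kauermann-Carroll, t(48 − p) |
|---|---|---|---|---|---|
| Main effects + strata | 8 | main (5%) | 8.1% | 7.9% | 4.6% |
| + two-way | 14 | main (5%) | 10.8% | 10.8% | 4.9% |
| + two-way | 14 | interaction (10%) | 17.5% | 17.7% | 10.1% |
| Full factorial | 19 | main (5%) | 13.8% | 13.9% | 5.0% |
| Full factorial | 19 | interaction (10%) | 21.1% | 20.8% | 9.7% |

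A direct exchangeable-GEE fit to 1,400 datasets gave 7.9% (p = 8) and 13.5% (p = 19) for main effects, and 20.7% for interactions. The inflation also persists at ICC 0.10 (7.9% and 13.9% for main effects with p = 8 and 19), at a base rate of 40% (13.5% with p = 19) and with unequal strata of 18/14/10/6 clinics (8.0% and 13.6%).

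**Alternatives.** A t reference with the uncorrected sandwich still gives 12.3% for main effects and 19.4% for interactions at p = 19. Mancl-DeRouen with t(48 − p) overshoots: 3.0%, 2.1% and 1.3% for main effects with p = 8, 14 and 19.

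**At least one false interaction among 11 (full factorial, null).** Uncorrected: about 90%. With Kauermann-Carroll and t(29): about 65%. Eleven independent tests at a correct 0.10 would give 1 − 0.9^11 = 69%.

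**Power after the correction.** At an odds ratio of 1.77 and N = 480, the noncentral t gives 78.5% (40 df) or 77.7% (29 df); the minimum detectable odds ratio is 1.79 or 1.80.

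**The case against.** The strongest reply is that the article never says the sandwich will be left uncorrected or referred to a normal distribution. Robust standard errors as a family include the bias-corrected versions, and the variant is commonly settled in a SAP. The quoted sentence also goes on to speak of a slightly wrong working correlation, where its claim is standard. This stands, and it makes the point conditional. It does not remove it: the article fixes the test and offers robust standard errors as what makes the inference right, and the ordinary form does not achieve that here.

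A reader might infer that the plan doubles or nearly triples its error rates. The documents do not support that as a general statement. For main effects it needs the 14- or 19-parameter model, and no section says that main effects are tested there. With main effects and strata only, the factor is about 1.6.

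A reader might also blame the standard errors for the whole 90% chance of a false interaction. Most of it is multiplicity from 11 tests at a level chosen deliberately; the correction takes it only to about 65%.

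Finally, Determining the Optimized Intervention lets costs, effect sizes and staff feedback weigh alongside significance. Point estimates are unaffected by the variance bias, and a false interaction does not by itself select a wrong package. That limits the harm, but it does not justify a test that fails to hold its stated level.

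**Conclusion.** The point holds conditionally. If the ordinary sandwich and a normal reference are used, every model that the text permits misses its stated level: about 8%, 11% or 14% for main effects, depending on the model, and about 18% to 21% for interactions. In the full factorial model the variance bias adds about 25 percentage points to the chance of at least one false interaction.

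The sizes rest on two-sided tests, clinic-level strata and the plan's 48 clinics of 12; they change little with the ICC, base rate or stratum sizes tried. Severity: should-fix, because the choice can be made before analysis without touching design or data. It is moot if the SAP already names such a correction.

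**What to change.** In Data analysis plans or the SAP:

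- List the terms of the model used for the main-effect tests and of the model used for the interaction tests.
- Specify a Kauermann-Carroll (or equivalent) bias-corrected sandwich with a t reference on 48 minus the number of regression parameters: 40 df for main effects and strata, 34 with two-way interactions, 29 for the full factorial. A t reference alone is not enough, and Mancl-DeRouen with these degrees of freedom is over-conservative here.
- Restate power at an odds ratio of 1.77 with N = 480 as about 78%, or the minimum detectable odds ratio as about 1.79 to 1.80.

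The cost is a few sentences and about two points of stated power; recruitment, data collection and allocation do not change. Multiplicity across the 11 interaction tests is a separate matter that this change does not address.

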### Data analysis plan for secondary and economic outcomes

For rigor, mediation will be tested as the product of the a-path coefficient (*a* = effect of X on M) and b-path coefficient (*b* = effect of M on Y). Additionally, the diagnosis of weak performing components and high-performing components will be determined by evaluating separate paths (a-path = X to M, b-path = M to Y). We will estimate the a-path, b-path, and indirect coefficients and their 95% confidence intervals via causal mediation approaches in M*plus,* which allows binary mediators and/or outcomes [142, 143] and can compute cluster-adjusted hypothesis tests for mediators, which is important given our study’s cluster-randomized design [144]. Reflecting the decision-priority framework and to minimize Type II error, α will be set at 0.05 for hypothesis tests. Mediators will be measured at the 6-month follow-up period to ensure the required ordering of variables.

Secondary exploratory analyses include identifying moderators of the intervention component-viral suppression relationship. Based on the *principle continual optimization*, moderation analyses allow understanding of *when* and *among what person characteristics* the component creates change. The optimized intervention can then be refined based on effect sizes that change based on a moderator of the component-outcome relationship. Potential clinic and participant moderators are shown in our conceptual model depicted in Fig. 2 and include variables such as sex, age, geographic location, ALHIV population size, HIV acquisition mode, and exposure to HIV/STI programs external to the study. Significant interactions will be further probed using simple main effects for categorical moderators and, for continuous moderators, changes in component-outcome effects at percentiles of moderators plus the Johnson-Neyman method [145]. Finally, additional exploratory analyses will assess moderated mediation by employing causal mediation methods to decompose the total component-outcome effect to evaluate whether the effect of the intervention component on the outcome is due to mediation alone, moderation alone, mediation and moderation together, or neither. Reflecting our decision-priority framework, tests of moderated mediation will be evaluated at α = 0.10.

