### Secondary and economic outcomes

We are using achievement of viral suppression as the outcome, defined as confirmed VL test < 1000 copies per mL at the 12-month follow-up assessment. This outcome was chosen because we aim to investigate the causal process and to meet the temporal sequencing assumption required for mediation and that any mediating effect, M, must occur prior to the evaluation of the outcome, Y, and after the delivery of each component, X. To meet the temporal sequencing assumption, we will collect data on all mediating variables during a second survey at 6-month assessment.

Cost-effectiveness will be determined using an activity-based ingredients approach to examine the costs of the component combinations to achieve a unit of effect across the primary outcome. The cost portion of the CEA will be measured during the 24 months that the intervention is delivered using the factorial design and the MOST framework.

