### Eligibility

A total of 576 ALHIV (aged 11–17 years) will be recruited from 48 health clinics. Adolescents’ inclusion criteria are: 1) An adolescent living with HIV (confirmed by medical report and aware of status); 2) living within a family; 3) being 11–17 years of age (at enrollment); 4) Prescribed ART; and 5) enrolled in ART care at one of the 48 health clinics in the study districts. Health clinics would be eligible if they: 1) have existing procedures tailored to adolescent adherence (including adolescent-specific clinic days and peer counselling) and 2) accredited by the Uganda Ministry of Health as a provider of ART within the study districts. Exclusion criteria include an adolescent’s inability to understand study procedures and participant rights as assessed during informed consent/assent process with the adolescent or parent. If the adolescent or adult caregiver presents with emergency needs (e.g., hospitalization), needed care will be secured, rather than study participation.

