### Survey and clinical data collection

Survey assessments will occur at baseline, 6-, 12-, 24-, and 36-months, and all assessments will take place in ICHAD’s private research field offices in Masaka; at satellite sites (MildMay, RTY- Uganda); or at the participants’ homes (if they request it and there is sufficient privacy to ensure confidentiality, or at clinics (in a private room) with each lasting about 60 min [105]. Flexibility in interview location has been critical to Suubi + Adherence and other ICHAD studies success to date, with approximately 40% conducted in research offices in Masaka, and 50% in satellite sites [105]. Assessments are administered orally however for questions measuring sensitive behaviors, computer assisted self-interviews will be administered [106]. Non-sensitive questions will be interviewer-administered using Qualtrics [106]. Viral load assessments occur at the same time points but not at the 6-month follow-up assessment. Surveys will be conducted in English or Luganda depending on participants’ English proficiency [106]. All interviewers will be fluent in both languages. In Table 1, we provide a list of standardized instruments that will be included in the main statistical analyses. All measures used have been or will be pre-tested and made appropriate for the local Ugandan context [106].

**Table 1 Tab1:** Survey, clinical, and costs data

**Variables Moderators**	**Measurement**	**Time Point (Months)**
1. Demographics 2. Age 3. Sex (assigned at birth) 4. Family: Orphan status, socioeconomic status, family composition/structure, caregiver educational level 5. Geographic location and exposure to outside HIV-related programs	Self-reported Questionnaire	Baseline, 6, 12, 24, 36

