**Mediators and Moderators**		
1. Financial literacy; 2. Financial management skills; 3. Engagement with financial institutions	Self-reported questionnaire Data from Bank Statements Self-reported questionnaire	6 months
1. Knowledge about ART 2. Internalized stigma 3. Sexual negotiation and communication skills 4. Mental health and HIV identity	Self-Report Questionnaire and Pill counts Social impact scale [107] Sexual Communication Scale [108] Condom negotiation scale [109] Beck Hopelessness Scale [110] and Center for Epidemiological Studies-Depression Scale (CESD) [111] & Negative Self-image sub scale of HIV Stigma Scale, [112] HIV-Positive Identity Questionnaire [113]	6 months
1. Problem solving of HIV care logistics 2. Self-esteem and social support 3. Engagement and retention in HIV care	Self-reported questionnaire Rosenberg Self-Esteem Scale [114] and Social Support Scale [115] HIV Index of Engagement [116, 117] and clinic records	6 months

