**Primary Outcomes**		
Viral load		Baseline, 12, 24, 36

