### Data sources

Data for the proposed study will be obtained through an eligibility screening checklist, and computer assisted, interviewer-administered structured questionnaires. Self-reported data via interviews will be collected at baseline and at all follow-up assessments from all participants. We will use self-report questionnaires with read-aloud procedures by professional trained staff to address issues of literacy. Multiple research assistants (RAs) will be hired to conduct assessments. To encourage truthful responding, we will remind participants that responses are confidential and explain to them the security system that makes it impossible to link a name to data. Each participant will complete a total of five interviews (one at baseline, then four follow-up interviews). One at 6 months (after delivery of intervention) then three 12 months apart (from intervention initiation).

The battery takes into account: 1) sensitivity to participant’s literacy (RAs read questions aloud and help fill out measures); 2) need for trust and rapport, and 3) use of local phrases and terms. In our previous work, participants completed these interviews without incident, often reporting positive experiences in being interviewed. Moreover, interview breaks and snacks will be provided and sensitive interviewers who are familiar with interview questions will facilitate the process.

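### Mediators are scheduled at 6 months, with temporal order as the only stated safeguard, so the non-randomized mediator-to-suppression path is open to baseline confounding; the baseline schedule must be reconciled

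*Protocol article*

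**What the plan says.** All references are to the Protocol article.

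**Mediator timing.** Data analysis plan for secondary and economic outcomes: "Mediators will be measured at the 6-month follow-up period to ensure the required ordering of variables". Secondary and economic outcomes: "we will collect data on all mediating variables during a second survey at 6-month assessment". Each of the three mediator rows of Table 1 gives 6 months only, for example "HIV Index of Engagement [116, 117] and clinic records 6 months". The same table does name baseline elsewhere: the demographic moderators are listed at baseline and every follow-up, and the viral load row reads "Viral load Baseline, 12, 24, 36".

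**A statement that points the other way.** Data sources: "Self-reported data via interviews will be collected at baseline and at all follow-up assessments from all participants". It does not say which scales are in the baseline interview.

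**Outcome of the mediation model.** Viral suppression, "defined as confirmed VL test < 1000 copies per mL at the 12-month follow-up assessment". This is a status at 12 months, not a change from baseline.

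**Entry criteria.** Eligibility requires "4) Prescribed ART; and 5) enrolled in ART care at one of the 48 health clinics in the study districts", together with confirmed HIV, age 11–17 and living within a family. Viral suppression is neither required nor excluded.

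**Covariates.** Data analysis plans names randomization stratum as the single covariate and says that all analyses are adjusted for it. The mediation section names no mediator-outcome confounder.

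**Use of the b-path.** Mediation is tested as the product of the a-path (component to mediator) and the b-path (mediator to outcome). The two paths are also evaluated separately, to tell weak components from strong ones.

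**The concern.** Randomizing clinics to components protects the a-path. It does not protect the b-path, because nobody is randomized to a level of stigma, depression, self-esteem, knowledge or engagement. An adolescent with high self-esteem at 6 months may have had it at baseline and may already have been suppressed then. If so, the 6-month mediator predicts 12-month suppression even when changing the mediator would do nothing.

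Placing the mediator before the outcome rules out reverse causation from the 12-month result, but it leaves this common-cause path open. The article gives temporal order as its only reason for the timing and states no other safeguard.

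Two features give the point weight. Testing mediators is one of the three listed primary aims, and the b-path is read on its own, so its bias matters even where the a-path is nil. Also, the collection schedule is set by the protocol: a baseline scale that was never administered cannot be recovered by a later analysis plan.

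**Working it through.** **1. Is there a plan figure to reproduce?** Not for this point. Power analysis gives a minimum detectable indirect-effect odds ratio of 1.80 for Aim 2, but no a-path, b-path or baseline-covariate inputs, so it cannot be rebuilt and does not bear on the question. The article gives no correlation between baseline and 6-month mediators, or between mediators and viral load. All such values below are assumptions, shown as ranges.

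**2. Large-sample check of the bias (n = 400,000).** X is the component, M0 and M6 are the mediator at baseline and 6 months, V0 is the baseline propensity to be suppressed, Y is suppression at 12 months, and e is independent standard normal noise.

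- M6 = 0.3·X + s·M0 + √(1 − s²)·e, where s is mediator stability (√(1 − 0.6²) = 0.8 at s = 0.6)
- V0 = c·M0 + e
- logit P(Y = 1) = 1.1 + 1.0·V0 + g·M0 + b·M6, giving about 71% suppressed

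The b-path is the logistic coefficient of M6, adjusted for X only.

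| s | c | g | Estimated OR when b = 0 | Estimated log OR when b = 0.30 |
|---|---|---|---|---|
| 0.6 | 0.3 | 0.2 | 1.28 | 0.50 |
| 0.6 | 0.3 | 0 | 1.16 | 0.41 |
| 0.3 | 0.2 | 0 | 1.05 | 0.305 |

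In the first row the true effect is overstated by 0.50/0.30 − 1 = 67%. In the last row the overstatement is 0.305/0.30 − 1 = 2%; there, omitting the strong predictor V0 pulls a logistic coefficient towards zero and offsets most of the confounding.

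In the first scenario, adjusting for M0 and V0 returns a log OR of 0.00 when b = 0 and about 0.29 to 0.31 when b = 0.30. Adjusting only for a yes/no baseline suppression indicator still leaves a log OR of 0.17 when b = 0, that is, an OR of exp(0.17) = 1.19.

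**3. Check at the trial's planned analysis size.** 480 participants in 48 clinics, cluster-robust standard errors, 400 replicates per scenario, true b = 0, and baseline suppression entered as a binary status. Assumed ranges: stability 0.3–0.6, correlation of baseline mediator with baseline viral status 0.2–0.4, OR of baseline suppression for the outcome 4–8, direct baseline-mediator log OR 0–0.3. These are somewhat wider than in step 2. The a-path is 0.3 SD unless stated.

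| b-path model | OR (true value 1.00) | Significant at 0.05 |
|---|---|---|
| No baseline adjustment | 1.04–1.37 | 10–86% |
| Baseline viral status only, baseline mediator has its own path to outcome | 1.06–1.17 | 9–30% |
| Baseline mediator and baseline viral status | 0.99–1.01 | 4–8% |

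- With stability set to zero, the unadjusted OR is 1.00 and 5% of runs are significant.
- With an a-path of 0.3 SD, both paths are significant in 9–79% of runs unadjusted and 3–8% adjusted.
- With an a-path of zero, both are significant in 2% of runs unadjusted. The b-path alone is still biased there.

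**The case against.** The strongest reply has four parts.

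**The scales may be given at baseline.** Data sources says that interviews collect self-reported data at baseline, and the 6-month visit is called a second survey. Table 1 is introduced as listing instruments for the main statistical analyses, so 6 months could be the analysis time point. This stands as a reason not to say flatly that no baseline mediator exists. It does not settle the matter: no statement places the mediator scales in the baseline interview, and Table 1 names baseline in other rows.

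**Baseline viral load is available.** Survey and clinical data collection says "Viral load assessments occur at the same time points but not at the 6-month follow-up assessment", and those time points include baseline. A reader might infer that the plan estimates the b-path without baseline viral load. The article does not say so. It gives no covariate set for the mediation models, and a fuller analysis plan may include it. That part of the reply holds, but it reaches only the covariate list: such a plan cannot supply a mediator that was not measured, and viral status alone left bias in step 2 and in those scenarios of step 3 where the baseline mediator acts on the outcome directly.

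**The consequence is limited.** A reader might infer that a biased b-path would put the wrong components into the optimized package. Determining the Optimized Intervention selects on component effects, costs, constraints, and staff and investigator feedback; the b-path is not listed. A false indirect effect also needs a non-zero a-path, and the a-path is randomized. Both limits stand.

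**The size is assumed.** No stability or correlation figure is given, and some mediators, such as knowledge and engagement, are meant to change. This is correct, and it is why only a range is offered.

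**Conclusion.** The concern holds in a limited form. The article contradicts itself, or is at least unclear, on whether mediators are measured at baseline. Its only stated safeguard, temporal order, does not remove baseline confounding of the b-path, and stratum adjustment does not do so either.

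The b-path can therefore be biased; that it will be is not shown. Under assumed stability of 0.3–0.6, a baseline mediator-to-viral-propensity coefficient of 0.2–0.3 and a direct baseline-mediator log OR of 0–0.2, a nil path appears as an OR of about 1.05 to 1.28 per unit, and a true log OR of 0.30 is estimated as about 0.31 to 0.50. With no mediator stability, a nil path shows no bias.

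The documents do not support the stronger statements that mediators are certainly unmeasured at baseline, that baseline viral load is left out, or that the final package would be wrong. The primary analysis of component effects on sustained suppression is not affected.

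**What to change.** 1. Reconcile Table 1, Secondary and economic outcomes, and the mediation analysis section with Data sources. State which mediator scales are in the baseline interview.
2. In Table 1, list at baseline and 6 months each mediator scale that can be measured before treatment. Bank-statement data from accounts opened by the programme have no pre-treatment value and stay as they are.
3. State that the mediation outcome model includes the baseline mediator and the already collected baseline viral load or suppression status, alongside the stratum adjustment already planned. Put the same terms in the mediator model, where they add precision. Baseline suppression status alone is not enough.
4. If baseline interviews were completed without a scale, adjust for baseline viral load and report that mediator's b-path as open to residual confounding.

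Cost: nil if the scales are already in the baseline battery, otherwise a few minutes at an interview that takes place anyway. Viral load needs no new collection.
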